# Study Protocol:

## Mobile Nudges to Increase Early Vaccination Coverage in Rural Areas – A Pilot Investigation in Ghana’s Northern Region

### Project summary

Despite major progress made in vaccination coverage overall, timeliness of vaccines remains a key concern in many settings. At the same time, access to mobile phones has increased rapidly, offering new opportunities to track and deliver health services. The main idea of this research project is to use these newly available mobile phone networks to simultaneously address two of the biggest bottlenecks in vaccine delivery: timely registration of births, and lack of maternal effort to get essential vaccines. To increase registration, we will train volunteers selected by each community to report new births via SMS to a central registration system, and send small monetary rewards via mobile phone to volunteers for this reporting. To increase vaccination coverage, we will send reminder messages directly to mothers, and will also test small monetary rewards as an incentive to complete recommended vaccinations. The vaccination encouragement designs will be tested through a small randomized controlled study in 15 selected villages in Ghana’s Northern region. The primary outcome variable for the pilot study will be the percentage of children with both completed BCG and initiated Polio vaccinations within the first four weeks (28 days) of their life.

### Rationale & background information

Despite major progress made in vaccination coverage overall, timeliness of vaccines remains a key concern in many settings [1, 2]. In Ghana, 95% of children receive BCG vaccination within the first two years of life [3], but only about half of these children receive the vaccine within the first 30 days after delivery, and more than 25% receive the vaccine more than 6 months after birth [3]. Early vaccination coverage is particularly low in settings where a large share of women deliver at home, as it is the case in Ghana’s Northern region, where only a minority of women seek out facilities for delivery [3]. According to the latest estimates, less than 50% of children in Ghana’s Northern region receive Bacillus Calmette–Guérin (BCG) vaccines within the first three months of their life, and less than 40% get polio vaccination, exposing a large number of infants to these diseases [2].

Recent research conducted in this region shows that the large majority of households have access to mobile phones now even in the most rural areas [4]. The main idea of the proposed project is to use these mobile phone networks to simultaneously address two of the biggest bottlenecks in vaccine delivery: timely registration of births, and lack of maternal effort to get essential vaccines. Evidence from India

suggests that even small rewards can often result in substantial increases in vaccine uptake [5] – we will test this hypothesis using mobile networks in rural areas of Northern Ghana.

### **Study goals and objectives**

The main objective of this study is to assess the extent to which mobile-phone based reminder or reward systems can increase early vaccination coverage. We will assess two specific interventions through the pilot study:

- 1) an *automated call and text system* which will first call mothers to highlight the importance of early vaccinations, and then send further text reminders (nudges) to mothers 3, 7 and 10 days after birth encouraging them to get their newborn vaccinated.
- 2) a *community volunteer-based system* that will provide small mobile credit rewards to both community volunteers and mothers for completing the early vaccinations within the first two weeks of newborn life.

### **Research Hypotheses (H1-3)**

H1: Nudging mothers through voice and text messages will increase early vaccination coverage.

H2: Nudging mothers through community volunteers and small rewards will increase early vaccination coverage.

Given that birth registration remains low in many parts of Ghana, we will also test a new community-based reporting model, under which volunteers appointed by the community will receive small rewards for reporting births in their communities. We will test the extent to which such a program improves birth reporting and registration:

H3: Providing small mobile-phone based incentives to volunteers selected by communities will result in accurate and timely reporting of births in rural areas.

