### *Community Volunteer Appointment and Birth Registration*

In all of the 10 intervention arm communities, we will implement sensitization meetings at the beginning of the study to explain the purpose and objective of the proposed work. We will then ask the community to appoint a local birth registration volunteer. Minimum qualifications for the local birth registration volunteer include the following: female; owns and has daily access to a smart phone with camera capability and the knowledge and ability to take photos and send SMS messages; is a member of the local community and in good standing with the community; speaks the local language fluently and has at least a minimum working knowledge of English and Dagbani; can read and write (local language fluency and working knowledge of English).

Candidate volunteers will be informed of the expectations of participating in the project, the project duration (6 months), the expected time commitment per week (approximately one hour per week in the incentive program areas and 30 minutes per week in the reminder-only program areas). They will then be invited to accept or decline the appointment as a birth registration volunteer. Birth registration volunteers who accept the appointment will undergo a standardized training to further inform them of the procedures and expectations of their role, and to provide practical advice on successfully engaging in their role.

Community volunteers will be expected to document and report all births in their communities to a central phone hotline which will be managed by study personnel. To motivate volunteers to report all births in their communities, and to compensate them for their efforts, they will be given a 2 cedis reward (USD 0.50) for each birth reported during the active study duration (6 months).

**Intervention arm A (“reminders only”)** focuses on automated voice and text messages sent to mothers. In this treatment arm, community volunteers will register all births in the community as described above.

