**All women who live in this community and have given birth to a live-born newborn in the previous week are eligible for enrollment.** As soon as possible after each birth, volunteers will contact the mother to briefly introduce the study and ask if they are interested in receiving vaccination-related information via voice messages and SMS on their phones. If the woman is interested, volunteers will describe the study purpose and procedures in more detail, answer any questions the woman has about participation, and guide the woman through the informed consent process. If mothers sign the written informed consent document (see *Informed Consent Reminder Intervention*), volunteers will ask the woman to provide a phone number of their choice at which they would like to be contacted to receive vaccine-related information and reminders. The volunteers will send the phone number provided by enrolled woman, together with a copy of the signed consent form, to a central study system.

An initial (automated) voice call will be made to all enrolled mothers to congratulate the mother on the birth and to highlight the importance of early vaccinations for their newborns. The message will also recommend that the mother take the newborn to get the BCG and Polio0 vaccine as soon as possible after birth if the newborn has not yet received these vaccines, ideally within two weeks after birth (as per Ghana national recommendations on immunization schedule). Additional reminder text messages will be sent to the phone number provided to the mother at 3 days, 7 days and 10 days of newborn life (as appropriate), reminding the woman to complete these vaccinations for her child. The text reminders will be short messages that reiterate the importance of early newborn vaccination for BCG and polio and will encourage woman to seek these vaccines for their newborns within the first two weeks of life if the newborn has not yet received them.

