Mothers will be informed that if they decide to participate, the volunteer may contact them to encourage them to vaccinate their newborn and to document the vaccination if the woman reports that one or both vaccinations have been completed. Volunteers may contact enrolled woman via phone voice message, call, text or in person at the household to provide information about early vaccination and to encourage the woman to vaccinate her child.

If the woman reports to the volunteer that she has completed the vaccinations, the volunteer will document vaccination status and dates of completion, take a photo of the vaccination card and/or record the date and location that each of the vaccinations was received. The volunteer will not conduct any further follow-up with women who report completion of both early vaccines.

Volunteers will report the successful completion of both vaccinations along with the photo and/or location and date to the central study hotline for verification. As proof of completed vaccination, the volunteer will either need to submit a picture of the vaccination card, or provide the date and location of each vaccination to the project phone line for verification. If both vaccines were successfully completed within the first two weeks of newborn life, the mothers and community volunteers will each receive a small reward of 2 cedis (0.50 UDS).

Mothers in the incentives arm will not receive automated voice messages or automated SMS text reminders for vaccination.

The study hotline and management of the mobile system for sending automated voice messages and SMS texts to enrolled participants will be managed by the local implementing partner, Innovations for Poverty Action Ghana (IPA Ghana). The appointment of community volunteers in both treatment arms, management of informed consent documents and supervision of the list of enrolled participants, verification and distribution of incentives to volunteers for registering births and vaccination completion for women in the incentives arm will also be managed by IPA Ghana.

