### ***Control arm***

No study-supported activities will be conducted in control communities during the active intervention phase. Women who give birth in these communities during the active intervention period will not be registered nor contacted by study volunteers nor receive study-generated reminders. No participants will be screened or enrolled in the control arm communities during the active intervention time period.

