## **Problems Anticipated**

This study involves minimal risks to subjects as described above.

One concern is that community volunteers may not report a sufficient number of births, so that reminder systems may not reach a sufficient number of women. We will closely monitor the monthly birth reports and will call or visit community volunteers in case birth reports are low or discontinued. A second concern is that mothers may not receive messages, or not listen to them. We will monitor the delivery status of messages carefully, and will coordinate with community volunteers if technical problems persist.

In both active treatment arms, it is possible that women could confuse the volunteers and message systems as mechanisms to access medical advice or medical care for newborns. We will inform women that volunteers and study staff running the reminder systems are not health professionals and that if they have a question or concerns about their baby's health they should visit a health facility.

It is also possible that participants in the treatment arms could mistakenly assume that the reminders or encouragement from volunteers cover all recommended care for their newborns and that if they complete the early vaccinations they have completed all recommended newborn care. We will inform all participants that there are other important services and vaccines that a baby should receive and that they should continue to seek care for the baby for other services and vaccines that are recommended.

In terms of potential adverse effects, one concern is that community volunteers may become too "enthusiastic" about the program, and exert too much moral pressure on mothers to get vaccinated. We will highlight this concern in our training. Only women will be invited to be volunteers to reduce potential pressure from male community members on female study participants.

One additional potential problem is that even if women visit their local health facility to request vaccinations for their children, the vaccinations may not be available or not be offered at the time point

when they visit. We will work closely with the local government health officials and health facilities to trouble-shoot and avoid these possible problems.

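### H1 and the reminder-only label credit the messages, but arm A versus control estimates a package of meetings, volunteer, enrolment contact and messages

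*Protocol*

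**What the plan says.** The Research Hypotheses section states "H1: Nudging mothers through voice and text messages will increase early vaccination coverage". Under Study goals and objectives, the first intervention is an automated call and text system, listed separately from a community volunteer-based system. Study Design Overview and Methodology call arm A the reminder-only arm, and its description says that it "focuses on automated voice and text messages sent to mothers".

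The section on volunteer appointment and birth registration gives arm A more than messages:

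- **Meetings.** "In all of the 10 intervention arm communities, we will implement sensitization meetings at the beginning of the study". Their stated aim is to explain the work, after which the community appoints a volunteer.
- **Volunteer.** She is trained and receives 2 cedis per birth reported. Expected time is 30 minutes a week in reminder-only areas and about one hour in incentive areas.
- **Enrolment contact.** Soon after each birth, "volunteers will contact the mother to briefly introduce the study and ask if they are interested in receiving vaccination-related information" by phone. If the mother is interested, the volunteer explains the study purpose, answers questions and takes written consent. Volunteer contact in arm A then stops.

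For the control arm: "No study-supported activities will be conducted in control communities during the active intervention phase". Study Design Overview adds that no volunteer is appointed there. Arm B has the same meetings and registration volunteer, plus volunteer encouragement and rewards, but "Mothers in the incentives arm will not receive automated voice messages or automated SMS text reminders for vaccination".

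**The concern.** A hypothesis should name what the randomised contrast estimates. H1 names the messages; the contrast that tests it differs in at least four elements at once. If the result is positive, the protocol as worded would have it reported as evidence that voice and text messages raise early coverage. The Literature Review presents the gap to be filled as evidence on text reminders in a low-income setting, and Expected Outcomes of the Study foresees a larger trial or incorporation into government programmes. Whoever designs that next step needs to know whether the meetings and volunteer are part of what was shown to work.

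**Working it through.** **1. Components by arm, from the protocol text.**

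| Component | Arm A | Arm B | Control |
|---|---|---|---|
| Sensitization meetings | yes | yes | no |
| Trained volunteer, 2 cedis per birth | yes | yes | no |
| Enrolment and consent contact after birth | yes | yes | no |
| Automated call and texts | yes | no | no |
| Volunteer encouragement; rewards for vaccination | no | yes | no |

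**2. What the arms identify.** Let s be the joint effect of the first three rows (taken as equal in A and B), m the effect of messages, and e the effect of encouragement plus rewards. Assume additivity.

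- A − control = s + m
- B − control = s + e
- A − B = m − e, which is the first line minus the second

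There are two independent contrasts and three unknowns, so m cannot be solved for. A − B removes s but leaves m − e. No analysis plan can recover s, because no arm has s alone.

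**3. Is s plainly zero?** The text does not allow that to be assumed. H2 counts community volunteers as part of the nudge. Volunteer time in arm A is 30/60 = half of that in arm B by the protocol's own estimate. The endline survey takes in recent mothers whether or not they joined the programme (Informed Consent), so arm A's coverage includes women who declined messages but lived with the meetings and the volunteer. None of this shows that s is large, or even positive.

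**4. The planned power belongs to s + m.** Inputs from Sample Size Calculation: 50% versus 80%, 20 children per cluster, intra-class correlation 0.05, power 0.9, alpha 0.05 (taken as two-sided).

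- Design effect = 1 + (20 − 1) × 0.05 = 1.95.
- Individual n per arm = [1.96√(2 × 0.65 × 0.35) + 1.2816√(0.25 + 0.16)]² / 0.30² = 51.01, rounded up to 52.
- 52 × 1.95 = 101.4, or 51.01 × 1.95 = 99.5 before rounding. The plan's 100 per arm reproduces.
- Effective n = 100/1.95 = 51.3, giving power 0.902.

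That power is for the total difference between arm A and control.

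**5. Illustration.** The values of s below are assumed; the protocol gives none. Set m = 0 and control coverage to 50%, with effective n 51.3 per arm. The table gives the probability of a significant result in favour of arm A, by the normal approximation and by a t reference with 8 degrees of freedom (10 villages less 2).

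| Assumed s (points) | Normal | t, 8 df |
|---|---|---|
| 0 | 0.025 | 0.025 |
| 5 | 0.07 | 0.07 |
| 10 | 0.17 | 0.15 |
| 15 | 0.33 | 0.28 |
| 20 | 0.54 | 0.46 |
| 30 | 0.90 | 0.84 |

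**The case against.** The volunteer layer is disclosed, not hidden. The project summary sets volunteer registration beside reminders, and elsewhere the protocol speaks of systems and platforms. Registration and consent are how arm A obtains phone numbers, so they are part of delivering the messages, and reminder-only can be read simply as marking the contrast with rewards. Contact in arm A ends after consent, and this is a pilot. All of that stands. It justifies testing a package and argues against adding an arm; it does not justify a hypothesis that names one part of the package.

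Several stronger readings are tempting, and the protocol does not support them:

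- **That the post-birth contact is a vaccination discussion.** It is described as a study introduction and consent procedure, and what is offered is information by voice message and SMS. Explaining the study purpose may cue the mother, but the text goes no further. That the contact is in person is an inference from the form being read aloud and signed or thumb-printed on paper.
- **That the meetings promote vaccination.** Their stated purpose is to explain the work, and the arm A volunteer is paid for reporting births.
- **That volunteers will prompt vaccination when messages fail.** Problems Anticipated says that the team "will coordinate with community volunteers if technical problems persist", but that sentence is about message delivery.
- **That H2 has the same fault.** H2 and the second objective already name volunteers and rewards together. Only the background sentence on small rewards, "we will test this hypothesis using mobile networks in rural areas of Northern Ghana", is looser than H2.

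**Conclusion.** The point holds as one of attribution. Arm A versus control is a sound randomised comparison of the whole package with no study activity. It does not identify the effect of messages, and H1, objective 1 and the reminder-only label claim that it does. A reader might go further and infer that the messages do nothing, or that the trial can show nothing about arm A; neither follows.

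No figure in the plan is wrong on this account, and there is no corrected sample size. The share of any gain due to messages cannot be bounded from the documents: it could be all of it, none of it, or more than all if the other parts worked against uptake. The probabilities above only show how the test would behave under assumed values. The identification argument assumes additivity and the same background effect in arms A and B; relaxing either adds unknowns and does not help.

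**What to change.** - Restate H1 and objective 1 as the effect of community sensitization, volunteer birth registration and enrolment contact, and voice and text reminders together, compared with no study activity.
- Keep reminder-only as a label if wished, but define it at first use as that package without rewards or continuing volunteer encouragement.
- State that A versus B compares two packages and does not isolate rewards from reminders.
- Leave H2 as it is. At most, align the sentence on small rewards in Rationale & background information with it.

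The cost is protocol wording and a narrower claim about messages. Villages, arms, sample size and data collection are unchanged. Isolating the messages would need villages with the meetings, volunteer and enrolment contact but no messages; that is a matter for the larger study the protocol anticipates.

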## Study Design Overview

The study will be designed as an open label cluster-randomized controlled study with three arms: a control arm, a reminder-only arm, and a reward arm. During the intervention phase community volunteers will be appointed to register all births in 10 randomly selected treatment communities. In each active treatment arm, an estimated 100 women across five villages will be enrolled in a proactive program. In intervention group A, participating women will receive reminders about vaccinations recommended at birth via mobile phones. In intervention group B, participating women will receive encouragement from a community-appointed volunteer to complete vaccinations recommended as well as a small cash reward for completing the recommended vaccinations. An estimated total of 200 women in the 10 treatment villages will receive one of the two study-initiated program interventions. No volunteer will be appointed to register births in the 5 control-arm villages and no woman in the 5 control-arm villages will be actively enrolled nor receive a pro-active program intervention during the intervention phase.

After the intervention phase is complete, an endline population-based household survey will be conducted in the 15 study villages to evaluate the effect of the intervention programs. The survey will enroll all consenting woman who have delivered a live-born baby in the last 12 months and reside in one of the 15 communities in the three study arms (10 intervention communities and 5 control communities). Based on a crude birth rate of 40 and an average village size of 100-1500 people, we estimate enrolling approximately 600-750 women in the endline survey. The endline survey will be used to compare the coverage of recommended early newborn vaccinations, and the proportion of births accurately and completely registered in each arm.

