### **Primary and secondary outcomes**

The primary study outcome is completion of early vaccination; we will consider a child as having successfully completed the early vaccination schedule if **the child has received the BCG vaccine and at least one dose of the polio vaccine within four weeks (28 days) after delivery**. We will additionally report the vaccine-specific coverage and the average age at vaccine receipt for each vaccine in each of the three arms.

The secondary outcome of the study will be the percentage of births identified via endline household survey that are reported by study volunteers. This outcome will be of particular interest for Ghana’s Birth and Death Registry, which is currently making major efforts to increase registration coverage in this region.

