***Endline survey:*** The endline questionnaire will be very simple and will only include questions on basic demographics, birth history and vaccination status of children. It is possible that a woman may feel uncomfortable answering some of these questions. Interviewers will inform woman that they don't have to answer any question they don't feel comfortable answering. Interviewers will attempt to conduct the interview in a setting that is semi-private so that the woman doesn't feel uncomfortable answering around others and isn't influenced by other household members or community members. However, the information collected in the survey does not include sensitive information and we believe it would be unlikely to cause significant harm or bring stigma to a woman if it was accidentally overheard by people in the household or community. It could be emotionally upsetting for a woman who has lost a child to be asked about the child and their medical care. Interviewers will be trained in respectful and compassionate interaction and refer woman to local support resources as available. The endline interview is anticipated to take no more than 15 minutes per household.

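### The protocol sets out to test whether the programme improves birth registration, but its only birth outcome is volunteer reporting to the study hotline, which is zero in control by design

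*Protocol*

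**What the plan says.** All references are to the Protocol.

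- **Aim.** Research Hypotheses (H1-3) starts from low birth registration in Ghana and continues: "We will test the extent to which such a program improves birth reporting and registration". The hypothesis that follows, H3, is narrower: small incentives to volunteers "will result in accurate and timely reporting of births in rural areas".
- **Planned comparison.** Study Design Overview says the endline survey will be used to compare "the proportion of births accurately and completely registered in each arm".
- **Outcome.** Primary and secondary outcomes defines one birth-related outcome: "the percentage of births identified via endline household survey that are reported by study volunteers". It then describes this as of interest to the Birth and Death Registry, which wants higher registration coverage.
- **Where reports go.** Under Community Volunteer Appointment and Birth Registration, volunteers are to "document and report all births in their communities to a central phone hotline which will be managed by study personnel".
- **Control villages.** Study Design Overview: "No volunteer will be appointed to register births in the 5 control-arm villages". The Control arm section confirms that births there are not registered by the study.
- **Survey content.** Ethical Considerations says the endline questionnaire "will only include questions on basic demographics, birth history and vaccination status of children". The Endline Survey section describes similar content, adding socioeconomic information and vital status, and also lists no registration item.
- **Analysis.** Data Management and Statistical Analysis applies logistic regression with cluster-robust standard errors to both the primary and the secondary outcomes.

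**The concern.** The aim names reporting and registration as two things, but only reporting is given a measurement. A child's civil registration status enters no outcome that the protocol defines. The per-arm comparison would therefore set programme villages, where volunteers are paid for each report, against villages where no report can exist.

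Two things are at stake. A difference between arms could be read as a gain in registration when no additional child has been registered. Conversely, if the programme did raise civil registration, the trial as described could not show it. The Registry, which the protocol names as an interested audience, would receive a figure that does not depend on the effect it cares about. The primary vaccination outcome is not affected.

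**Working it through.** **1. What the contrast depends on.** Let r be the share of births that volunteers report in programme villages, and R the share of births entered in the civil registry.

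- Outcome in programme villages: r
- Outcome in control villages: 0 (no volunteers)
- Contrast: r − 0 = r

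R appears nowhere. Whatever happens to R in either group, the contrast is unchanged.

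**2. Both readings of the word *register*.**

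- If it means civil registration, the comparison in Study Design Overview has no described measurement.
- If it means the study's own register, the comparison is measured, but its control value is 0 by design.

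Neither reading gives a test of improved registration.

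**3. Inputs for the size of the problem.** The protocol gives no figure for this outcome, so the cluster inputs come from Sample Size Calculation.

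- Births per village in six months: 1000 × 40/1000 × 0.5 = 20, as the protocol states.
- Intra-class correlation: 0.05.
- The protocol's own sample size (vaccination outcome, 50% vs 80%, power 0.9, alpha 0.05 taken as two-sided) reproduces: 52 per arm × design effect [1 + (20 − 1) × 0.05 = 1.95] = 101.4, so 102 against the stated 100.
- Villages: 10 programme, 5 control.
- Reporting share r: not given, so shown as a range.

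**4. Test against the structural zero, with civil registration unchanged.** There were 20,000 simulated trials. Village reporting rates were drawn from a beta distribution with parameters 19r and 19(1 − r), which gives a correlation of 0.05, with 20 births per village. Control was fixed at 0. The test was a pooled t-test on village proportions (10 + 5 − 2 = 13 degrees of freedom), two-sided 5%.

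| Assumed r | Share significant |
|---|---|
| 5% | 19% |
| 10% | 69% |
| 20% | 99% |
| 50% | 100% |

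As a check without simulation, take one programme arm against control, 5 villages each. If every programme village has at least one report, the exact two-sided permutation p is 2/252 = 0.008.

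Under the protocol's logistic model, zero events in control also mean that the odds ratio against control has no finite estimate.

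**5. The same test on a measured registration status.** If civil registration were asked in all 15 villages, the same village-level test would behave as follows (registration rates are assumed; the protocol gives none).

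| Control vs programme | Share significant |
|---|---|
| 30% vs 30% (no effect) | 5% |
| 30% vs 50% | 61% |
| 30% vs 60% | 91% |

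This contrast responds to registration and holds its error rate. Power for a 20-point gain is only moderate.

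**The case against.** **The hypothesis is only about reporting.** This stands. H3 mentions neither civil registration nor superiority over control, and for completeness of reporting the defined percentage is suitable. The fault lies in the sentence introducing H3 and in the per-arm comparison in Study Design Overview.

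**Registration mostly means the study's own register.** Much of the protocol does use the word that way, including the project summary and the description of the volunteers' task. On that reading the comparison is the defined outcome, but it is then a comparison with a built-in zero. The references to low registration in Ghana and to the Registry can only mean civil registration, so the two senses still need separating.

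**Stronger readings the documents do not support.**

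- A reader might infer that the survey asks nothing about registration. The questionnaire is an attachment not shown, and the Endline Survey section includes birth information that is not itemised. One can say only that no such item is described and that the exclusive list in Ethical Considerations names none.
- A reader might infer that the trial has a rule declaring success when programme arms exceed control. No such rule is stated. The support for a contrast is the per-arm comparison together with the regression model.
- A reader might infer that a handful of reports is enough for significance, since Fisher's test of 9/200 against 0/100 gives p = 0.032. That ignores clustering. At this 4.5% rate the village-level test is significant in only about 14% of simulations.

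**The simulation restates the definition.** Largely true. The percentages are not the error rate of a specified test, and the t-test is not the planned model. They show only how little reporting would be needed to produce a difference.

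**A registration outcome would test an effect with no described route.** No section forwards reports to the Registry. That is a fair argument for narrowing the aim rather than adding an outcome, and the fix allows for it.

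**Conclusion.** The point holds for the stated registration aim and the per-arm comparison. The defined outcome validly describes completeness of volunteer reporting in the 10 programme villages. Its contrast with control is fixed by design and cannot support a conclusion that registration improved, whichever sense of the word is meant.

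The conclusion itself is logical and needs no assumed rate. The 69% and 99% figures rest on assumed reporting shares of 10% and 20%, 20 births per village, a correlation of 0.05 and a village-level t-test. The matter concerns a secondary aim and should be settled before the endline survey, because a registration item cannot be recovered by analysis afterwards.

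**What to change.** Choose one of two routes.

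**Narrow the aim.** In Research Hypotheses, remove the claim to test improved registration. In Study Design Overview, remove the per-arm registration comparison. Report the volunteer-reported percentage descriptively in the 10 programme villages, with a cluster-adjusted confidence interval and no comparison with control. State the conclusion as completeness of volunteer reporting. The cost is wording only.

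**Keep the registration aim.** Add one item per birth to the endline survey in all 15 villages: whether the birth is in the civil registry, by certificate seen or mother's report. Amend the content list in Ethical Considerations. In Primary and secondary outcomes, make this the between-arm registration outcome for births in the intervention period, and keep the volunteer-reported percentage as a descriptive figure for programme villages. The cost is one question in an interview of 10-15 minutes that is already planned. The limits are reliance on maternal report where no certificate is seen, and moderate power (about 0.61 for 30% vs 50%, assumed rates).

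If the questionnaire already contains such an item, the outcome definition and the content list should say so.
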